### TiM-C Mechanisms of Action

In-depth case studies will be used to explore how HCPs use the data from TiM-C during clinical appointments and MDT meetings, which will enable an investigation into TiM-C’s mechanisms of action. Yin [30] suggests that 5 case studies are appropriate for complex interactions and 3 for literal replications. Therefore, a collective case study approach will be adopted using 5 MND centers. Within each case study, data will be collected relating to how TiM-C is used during 3 clinical appointments and 3 MDT meetings.

A combination of data collection techniques will be used, including focused ethnography, consisting of observations and field notes within clinical appointments and MDT meetings, alongside short questionnaires, and related document analysis. Information from the other elements of this process evaluation will also be incorporated into the case studies (eg, engagement data).

Members of the research team will conduct direct, nonparticipant observations of 3 clinical appointments and 3 MDT meetings. The same researcher will take field notes and potentially ask follow-up questions after the appointment or MDT meeting has finished. The researcher will either attend such activities physically or join virtual meetings. Appointments and MDT meetings will be audio-recorded and transcribed verbatim for analysis. Framework analysis will be used to analyze the transcripts and field notes.

A short, bespoke questionnaire was created to explore how HCPs perceived the use of the TiM-C data during MDT meetings. The questionnaire includes items on the trustworthiness of TiM-C data and whether and how the HCP acts on the data. All HCPs attending the MDT will be asked to complete this questionnaire after the meeting or appointment has finished.

Local HCPs and researchers will collect other documents relating to the use of TiM-C for the people with MND discussed at the clinical appointments or MDTs (eg, TiM-C messaging data, clinical notes, and emails) and securely transfer them to the central research team for analysis. Only data relating to TiM-C will be used. This information is necessary to identify how TiM-C data is used to support people with MND and caregivers outside of meetings. Farmer et al [25] triangulation protocol will be used to analyze the data set, due to the large amount of data involved, collected from multiple sources. Each case study will be analyzed separately before similarities and differences are considered in cross-case comparisons.

### TiM-C Economic Evaluation (WP4)

This WP includes a health economic analysis of the TiM-C system, as it is implemented in MND specialist centers and networks across the United Kingdom. A cost-consequence analysis [31] will form the primary economic evaluation because TiM-C is a complex digital intervention with multiple possible effects, including both health and nonhealth outcomes, which makes the creation of a single measure difficult. A budget impact analysis [32] will also be conducted, to help future health care commissioners understand how the implementation of TiM-C may affect expenditure under different circumstances.

The cost-consequence analysis will only focus on costs for intervention delivery, as TiM-C is not designed to replace any part of usual care (ie, TiM-C will incur costs in addition to usual care, rather than accrue cost-savings). Per patient and caregiver costs incurred from the need for a HCP to regularly review user scores, will be calculated by asking HCPs to estimate how long it takes to review the account of a single user. This will be combined with unit costs of health, accessed from the Personal Social Services Research Unit. These will be combined with the central cost of TiM-C per MND service, which is already known, in addition to HCP time to receive the necessary training. Outcomes will be taken from the process evaluation and presented alongside the per-user cost of TiM-C to aid comparison.

A budget impact analysis will be conducted using the costs calculated as part of the cost-consequence analysis described above. Engagement data from the process evaluation will then be used to describe the cost of TiM-C for the MND center (in terms of HCP time and system cost) under different review protocols. For example, TiM-C does not dictate how often HCPs should review the system. The more often TiM-C is reviewed and the higher the user engagement from people with MND and caregivers, the more HCP time will be needed and the higher the associated costs. This analysis will display these different circumstances to aid health care commissioners in understanding the affordability of the TiM-C service.

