## Introduction

Motor neuron disease (MND) is an incurable disease, that causes progressive weakness of muscles involving the limbs, speech, and swallowing, leading to progressive disability and eventual respiratory failure. In the United Kingdom, there are approximately 5000 people with MND at any one time [1]. The average life expectancy following diagnosis is 2 to 3 years but the course of MND can vary from only a few months to over 10 years. The distress and burden of the disease affects people with MND, their family, and caregivers and the relenting progression of disability causes social, emotional, and financial strain [2,3].

In the United Kingdom, multidisciplinary teams (MDTs) deliver specialist MND care through MND Care Centers or care networks across the country. Expert health care professionals (HCPs) monitor symptoms and offer interventions such as Riluzole, which can improve survival by approximately 2 to 3 months [4], gastrostomy feeding to promote good nutrition [4], or treatment of respiratory failure with noninvasive ventilation, which improves both quality of life and life-expectancy [5]. Attendance at specialist MND clinics has been reported to improve survival independent of these other interventions [6,7]. Traditionally, clinics are held at regular fixed intervals, approximately 3 months apart.

Despite the potential benefits of MDT care, this model is not always sufficiently responsive to the needs of patients because these can change rapidly, and therefore, can require people with MND and their families to undertake progressively more difficult journeys to the clinic at a time predicted by the clinician at their last meeting. Given the burden associated with traveling to the clinic, it is important that visits occur when they are most needed. Conversely, some people with MND whose needs may not change considerably over time, may not benefit from a clinic appointment every 3 months.

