From the perspective of individuals involved in the approval of National Health Service (NHS) services, what are the barriers and facilitators of approving TiM-C at scale?What are the unmet needs of people with MND, their caregivers, HCPs, MND researchers, and industry?How can TiM-C and TiM-R be developed to support end user needs?Does the use of the TiM-C service result in better MDT care for people with MND and their caregivers?What are the costs associated with the TiM-C service and how do they affect health care expenditure?

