## Methods

### Design

The design of this project was based upon multiple frameworks and guidelines, which have helped develop a logic model, consider outcomes, and data collection methods. These include the MRC framework for the development and evaluation of complex interventions [14], National Institute for Health and Care Excellence Evidence Standards Framework [15], Person-based approach to intervention development [13], and Non-adoption, Abandonment, Scale-up, Spread, and Sustainability (NASSS) [16]. A total of 14 sites will collect data, however, some work packages (WPs) will only use a subset of sites (eg, WP1 only collects data from 5). The project has 4, interconnected WPs, which answer the research questions above:

Governance approval strategy development (research question 1)TiM-C and TiM-R codevelopment (research questions 2 and 3)TiM-C process evaluation (research question 4)TiM-C economic evaluation (research question 5)

Through the NASSS framework and the collection of other data in the 2nd and 3rd work packages (described below), we will collect information that can be used to identify barriers that affect TiM-C and TiM-R implementation and use. Throughout the study, using an implementation science lens, we will address identified barriers to facilitate the uptake of the TiM system, using methods suggested by Cane et al [17]. We will document any adaptations made to our governance approval strategy or the TiM intervention.

To reduce the number of under-served groups within this project, the research team will aim to involve a diverse range of participants throughout the entirety of this study and overcome known barriers to participation [18]. This will include remote research activities to reduce the need to travel, support for caregivers to enable participation, and continual data monitoring to ensure representative inclusion of different ages and genders.

Each of the 14 sites involved in this study will be given permission to mildly modify research activities to enable people with different abilities or circumstances, who meet the eligibility criteria, to participate in any and all parts of the study they want to. For example, modifying consent or data collection procedures to enable the participation of people with MND and caregivers who are physically unable to complete documents, or questions being shared ahead of an interview to allow participants who have difficulty communicating time to prepare recorded answers.

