TiM-C also automatically collects the number of times an HCP logs into the system and sends feedback or resources to people with MND and caregivers. These data will be aggregated to calculate how often the TiM-C system is reviewed and used to send information to people with MND and caregivers.

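### WP4 yields the gross delivery cost of TiM-C, probably understated because staff response time is not costed, and not its net effect on health care expenditure

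*Protocol article*

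**What the plan says.** The Introduction poses research question 5 as "What are the costs associated with the TiM-C service and how do they affect health care expenditure", and the Design section gives it to WP4 alone: "TiM-C economic evaluation (research question 5". The abstract describes the aim of WP4 more broadly, in terms of costs and benefits and of cost-benefit.

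The WP4 section sets the cost scope: "The cost-consequence analysis will only focus on costs for intervention delivery, as TiM-C is not designed to replace any part of usual care". It adds that "TiM-C will incur costs in addition to usual care, rather than accrue cost-savings". Three components are named:

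- staff review time, "calculated by asking HCPs to estimate how long it takes to review the account of a single user" and valued with published unit costs;
- the known central system cost;
- staff time for training.

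Outcomes from the process evaluation are to be set beside the per-user cost. The budget impact analysis is introduced as a way for commissioners to see how adopting TiM-C could change spending. It takes its costs from the cost-consequence analysis and varies review frequency and user engagement.

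The Engagement section says that the system automatically counts how often an HCP logs in and "sends feedback or resources to people with MND and caregivers".

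**The concern.** Two gaps separate the stated aims from the quantity that WP4 will estimate.

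First, the aims speak of expenditure and of cost-benefit, while the costing covers delivery only. That TiM-C is not meant to replace usual care is a statement of intent. It does not show that use of usual care stays the same, and other sections leave the matter open. The Introduction notes that some people with stable needs "may not benefit from a clinic appointment every 3 months". WP3 repeats a yearly survey to see how MDT care has changed, and asks HCPs whether they act on the data. The Discussion says that WP3 and WP4 will gather data on the effect of TiM-C on service provision.

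Second, the delivery cost itself appears incomplete. Answering a user or sending material after reading a score is staff work that TiM-C creates. No time for it is named.

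At stake is how commissioners read the result. A gross figure could be taken for the effect on spending, with an error of unknown sign: too low if TiM-C leads to extra contacts, too high if visits are avoided. Within the delivery cost, the likely error runs one way, towards too low.

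**Working it through.** The plan gives no cost figure to reproduce, so the check compares what the aims require with what WP4 will supply.

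**1. Net effect on expenditure.** Let D be the delivery cost, and for each usual-care item k let Δu_k be the change in use and c_k the unit cost. Then

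change in expenditure = D + Σ (Δu_k × c_k).

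- D, as listed in the WP4 section, is system + training + review time.
- Δu_k is neither measured nor costed anywhere in the document. The WP4 section treats TiM-C as purely additive and without savings.

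With the sum set to zero, the result is D, which is positive by construction. WP4 cannot show a saving, nor an induced cost outside D. The budget impact analysis takes D as its input and changes only the amount of review and engagement, so it has the same property.

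**2. Scale of what would go unseen.** The Introduction puts clinics about 3 months apart: 12 / 3 = 4 visits a year. One visit added or avoided per user per year is 1 / 4 = 25% of clinic visits. This is a share of visits, not of expenditure, and the documents give no evidence that such a change occurs.

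**3. Completeness of D.** Per user, the staff cost that recurs should be

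(reviews × minutes per review + responses × minutes per response) × unit cost per minute.

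| Input | Source in the plan |
|---|---|
| Minutes per review | HCP estimate (WP4) |
| Frequency of review | Log-in counts (Engagement) |
| Responses sent | System counts of feedback and resources (Engagement) |
| Minutes per response | Not named |
| Unit cost | Published unit costs (WP4) |

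Only one input is missing. If r is minutes per review, p the number of responses per review and t the minutes per response, the omitted share of this recurring staff time is p·t / (r + p·t). It is above zero whenever any response is sent and its time is not already counted within the review. The documents give none of r, p or t, so I put no percentage on it.

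**The case against.** The strongest defense is that the restriction is declared openly and with a reason. Read literally, research question 5 asks how the costs, not TiM-C as a whole, bear on expenditure. WP4 answers the first half, and the budget impact analysis describes the center's own outlay for the second. The Introduction presents TiM-C as a supplement to traditional care, which agrees with the additive framing, and its remark on 3-monthly visits is background, not a prediction of fewer visits. A cost-consequence analysis also places effects beside costs, so service change is studied in WP3, though mostly qualitatively and not in money.

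Most of this stands. A reader might infer that WP4 fails to answer research question 5, or that the protocol declares every other cost unchanged. The documents support neither: the first half of the question is answered, and the text rules out replacement and savings without mentioning induced contacts. What remains is that the budget impact aim and the abstract's cost-benefit wording promise more than a gross cost to the center.

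On response time, it can be said that engagement data feed the budget impact analysis and that the full plan may define a review broadly. That is possible, and for this reason the understatement is called likely, not certain. But the article names the one time input to be elicited, and it is the time to review an account.

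**Conclusion.** The point holds in a limited form. As written, WP4 estimates the gross delivery cost of TiM-C and cannot speak to its net effect on health care expenditure, because change in usual care is fixed at zero by assumption and the budget impact analysis inherits this. The explicit statement of scope makes this a design choice, not detail lost in a condensed article.

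The delivery cost is likely understated, on the assumption that response time is not already included in what HCPs report as review time. Neither gap can be sized in money from the documents. The direction of the first is unknown, and that of the second is downward.

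This calls for an inexpensive improvement and does not invalidate WP4.

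**What to change.** 1. **Cost the responses.** When HCPs are asked to estimate review time, also ask for minutes per response. Multiply by the logged counts of feedback and resources sent, divide by the number of account holders for a per-user figure, and carry it into the cost-consequence table and the budget impact scenarios. Define review and response so that no minute is counted twice. The cost is one extra survey item and a less favorable cost figure.

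2. **Match the wording to the estimate.** In research question 5, the abstract's fourth objective, its cost-benefit phrase and the budget impact aim, refer to the gross delivery cost to the MND center. State that no conclusion on net expenditure can be drawn. This costs wording only.

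3. **Optional.** Add budget impact scenarios in which usual-care use moves up or down from about four clinic visits a year, labeled as assumptions.

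I would not add a count of appointments for 12 months before and after account creation. With progressive disease and an average life expectancy of 2 to 3 years, an uncontrolled comparison would be confounded by progression and death. The Nonexplicit Consent section also limits routine data used without explicit consent to the study of engagement.

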### Participants

Participant numbers are provided within each WP and each section of the process evaluation. Where numbers are not provided, we will recruit everyone who meets the below eligible criteria (Textbox 1; eg, The PREM described in the section “Service impact of TiM-C upon MDT care” and the MND service will be sent to every individual with MND at each site). To be as inclusive as possible, there are no exclusion criteria.

Eligibility criteria for each participant group.Patient inclusion criteria:Aged 18 years or olderDiagnosis of clinically definite, lab supported, clinically probable, or possible motor neuron disease (MND) by the El-Escorial criteria and additionally the Progressive Muscular Atrophy variant where appropriate investigation has excluded mimics of MNDCapacity to give informed consentHas been invited to create a TiM-Care (TiM-C) account at least 1 month agoCan understand written/verbal EnglishCaregiver inclusion criteria:Aged 18 years or olderCapacity to give informed consentHas been invited to create a TiM-C account at least 1 month agoCan understand written/verbal EnglishHealth care professional inclusion criteria:Health care professionals (HCPs) who provide support to people with MND, including medics, specialist nurses, dietitians, speech and language therapists, physiotherapists, occupational therapists, health care assistants, etc.Part of an MDT that has used the TiM-C system for at least 1 monthCan understand written/verbal EnglishMND research inclusion criteria:Aged 18 years or olderAny researcher who has previously or is currently conducting research with people with MND, their caregivers, or HCPs.Can understand written/verbal EnglishIndustry staff inclusion criteria:Aged 18 years or olderCurrently or recently (within last year) used by an industry organization that has conducted clinical research involving people with MND. This includes clinical trials, questionnaire-based studies, qualitative research, or telehealth research.Can understand written/verbal English

### Consent

All potential participants to each WP will be provided with written information about the nature and objectives of the study in the form of a Participant Information Sheet and given a minimum of 24 hours to decide whether to take part. However, a participant can consent immediately if they wish. Potential participants will also be given the opportunity to discuss the research with the relevant researcher and ask questions either in person or via contact details supplied in the Participant Information Sheet. Potential participants will be reminded that their participation is entirely voluntary and that they have the right to withdraw at any point (without it affecting the service provision for people with MND). Formal written consent will be obtained for all research participants, the process for which will be adapted for those participants unable to physically provide this. Consent may be taken remotely by verbally recording the participant, only if necessary. The consent procedure will be completed by the researcher/interviewer prior to any interview or observation. They will explain the study and make sure each person fully understands what they are agreeing to.

For the quantitative elements of the study, participants can immediately complete any questionnaires they have consented to. For the qualitative elements of the study, the local teams will pass on their contact details to the central research team. The research team will then contact the potential participants to provide them with more information about the study. Where relevant, the next step will be for the researcher to organize a mutually convenient time and place for the interview. Participants will not be offered payment for taking part in this study. Should interviews be conducted face-to-face, reasonable travel expenses will be reimbursed for participants.

Within the MDT observations, there is the possibility that some HCPs consent to be observed, whereas other HCPs do not provide this consent. In such a situation, the observation will still continue and be recorded. However, all instances where a nonconsenting HCP speaks will be removed from the transcript and any identifiable information about nonconsenting HCPs, such as names or job titles, will be removed. Nonconsenting HCPs will not be asked to complete a questionnaire.

### Nonexplicit Consent

Within the engagement section of the TiM-C process evaluation, this study proposes to analyze data on people with MND and their caregivers, which has been collected as part of running the MND clinical service. This data will only be used to investigate engagement with TiM-C and facilitate the exploration of reasons for the engagement and nonengagement with the TiM-C service.

As this data is collected as part of the standard running of the MND service, explicit consent will not be sought from people with MND and their caregivers before this data is analyzed. All individuals who have opted out via the national data opt-out service will have their data removed from this analysis. The legal basis for the use of this data is to improve or benefit health and care by monitoring the use of this novel intervention to investigate how effective it is.

### Ethical Considerations

This study was approved by the Health Research Authority and NHS Research Ethics Committee (reference number: 22/NI/0192). Informed consent is (or waiver thereof) and the process used to obtain this, is fully described in the section above. All data are anonymized, with participants being given a number (quantitative) or pseudonym (qualitative). Participants were given the choice of their own pseudonyms. No compensation or remuneration was provided as an incentive for any WP described within this protocol. However, reimbursement for reasonable expenses incurred (eg, travel to interviews) was provided to participants.

